## Abstract

**Background:**

Artificial intelligence (AI) has the potential to transform chest radiography interpretation by enhancing diagnostic accuracy, identifying subtle findings, reducing errors, and helping prioritize patient care. Although chest radiography remains a cost-effective and widely used imaging tool, its effectiveness is limited by overlapping anatomy and variability in clinical expertise. Integrating AI can help overcome some of these challenges, especially in resource-constrained settings. However, robust validation in real-world clinical contexts is essential before widespread implementation. This study protocol evaluates whether AI assistance improves general practitioners’ ability to detect radiographic findings on chest radiography in adults with respiratory complaints or those undergoing treatment for respiratory diseases compared with unaided interpretation. Potential benefits include increased diagnostic safety, higher physician confidence, more efficient workflows, and expanded access to expert support in underserved areas.

**Objective:**

This study aims to evaluate whether AI assistance enhances physicians’ ability to detect key radiographic abnormalities, including consolidation or pulmonary opacity, pneumothorax, atelectasis, pleural effusion, and cardiomegaly. The primary outcome is the difference in physicians’ diagnostic accuracy (per examination) when assisted by the AI tool compared with usual practice, using expert radiologist consensus as the reference value.

**Methods:**

This study is a protocol for a multicenter, stepped-wedge, cluster-randomized clinical trial following the CONSORT-AI (Consolidated Standards of Reporting Trials-Artificial Intelligence) extension and SPIRIT-AI (Standard Protocol Items: Recommendations for Interventional Trials-Artificial Intelligence) guidelines. The intervention involves the diagnostic support solution for chest radiography, Lung Analysis (LuAna), an AI-powered chest X-ray interpretation tool developed in partnership with the Brazilian Ministry of Health. Across 9 cities in Brazil, clusters will transition monthly from unaided chest X-ray interpretation by general practitioners to AI-assisted interpretation, with performance benchmarked against thoracic radiologists. The stepped-wedge design ensures that all clusters receive the intervention, reflecting real-world coordination, enhancing acceptability, improving statistical power, and strengthening causal inference through repeated measures. Diagnostic performance will be compared with a reference standard established by thoracic radiologists.

**Results:**

This project was funded in October 2024 (following ethics approval by the institutional review board). Data collection commenced in January 2026 and is projected to be completed by September 2026, marking the end of the trial period. As of November 2025, 3 centers were fully prepared for enrollment initiation. The LuAna clinical trial is currently ongoing, with data analysis (including statistical analyses) forecasted to be finalized by November 2026. Results are expected to be published by January 2027.

**Conclusions:**

This intervention is expected to enhance clinical decision-making by supporting earlier treatment initiation and more appropriate diagnostic pathways for patients with respiratory symptoms while maintaining a favorable safety profile and high physician usability. Findings from this trial will provide real-world evidence on the clinical utility of AI-assisted chest radiography. If effective, LuAna may leverage its scalability and equity advantages to become a replicable model for integrating AI into routine imaging workflows worldwide, especially in regions with limited access to specialist care.

## Introduction

Artificial intelligence (AI) is increasingly recognized as a transformative tool in global health care. In high-income countries, AI is already enhancing diagnostic accuracy, supporting clinical decision-making, accelerating research, and improving health system management [1]. However, most low- and middle-income countries (LMICs) have yet to benefit from these advances [2]. In LMICs, AI holds significant potential, enabling better care, strengthening disease surveillance, expanding telemedicine, and improving medical imaging interpretation [2]. Integrating AI in these settings could accelerate progress toward the United Nations Sustainable Development Goals [3] and promote fair access to advanced health care technologies [4].

Chest radiography is the most commonly performed imaging test worldwide and remains vital for assessing cardiothoracic conditions [5,6]. It accounts for a significant portion of the billions of radiologic examinations conducted globally each year [7]. Chest X-ray (CXR) is still a cornerstone for diagnosing pulmonary diseases, particularly where advanced imaging is unavailable. It is accessible and cost-effective [8], but its interpretation can be hindered by overlapping anatomical structures, technical limitations, and variable reader expertise [9,10]. These limitations are more pronounced in LMICs, where shortages of trained specialists contribute to diagnostic delays and errors [11].

Given its high volume and clinical relevance, CXR imaging has become a key target for developing deep-learning tools to improve diagnostic accuracy and workflow efficiency [8,12]. AI offers promising solutions by automating image analysis and supporting frontline physicians in clinical decision-making. Advances in convolutional neural networks have enabled the development of AI tools with diagnostic accuracy comparable to radiologists for key findings, such as pneumonic consolidation, pneumothorax, and pulmonary nodules [4,6,13]. A recent study shows that an AI system using deep convolutional neural networks could reliably analyze chest radiographs to identify features of COVID-19 pneumonia, such as ground-glass opacities and consolidation, offering a faster, cheaper alternative to computed tomography (CT) scans [14]. Though accuracy decreased for non–COVID-19 abnormalities poorly represented in the training data, it remained useful for screening and confirming typical cases, with suspicious cases requiring a CT scan. Ongoing improvements and diverse data will boost its performance, making AI-assisted CXR evaluation practical and cost-effective. However, 2 persistent challenges remain: (1) integrating AI into real-world clinical workflows and (2) providing effective support for nonradiologist physicians in resource-limited environments.

Rigorous validation is essential before implementing AI tools. This process requires not only comparisons with expert diagnoses to establish accuracy and reliability, but also prospective evaluation in real-world clinical settings to confirm safety, usability, and cost-effectiveness. Despite being resource-intensive, such efforts have already shown tangible benefits: in lung cancer pathways, adjunct AI for CXR interpretation can reduce missed cancers and is expected to be cost-saving compared with radiologist-only reporting [15,16].

In tuberculosis (TB) control, economic models from Pakistan indicate that AI-based computer-aided CXR triage can reduce diagnostic costs by approximately 20% to 40% compared with standard smear- or GeneXpert-based algorithms, primarily by limiting unnecessary confirmatory testing while maintaining case detection [17,18]. Cost-effectiveness is strongest in moderate- to high-prevalence settings and high-throughput programs, where economies of scale reduce per-screen costs. Similarly, evidence from Zambia shows that comprehensive radiography-based case-finding interventions can improve detection and achieve favorable incremental cost-effectiveness compared with passive case detection [19]. Overall, economic value is driven by prevalence, screening volume, and test cost differentials, with added system-level benefits including earlier diagnosis and more efficient resource allocation [15-19].

Despite the promising retrospective performance of AI models for CXR interpretation, their real-world effectiveness remains uncertain when deployed across large, heterogeneous health systems. Models trained and validated in limited or single-center datasets frequently experience distribution shifts that degrade performance when applied to different populations, imaging equipment, and clinical workflows [20]. A continental-scale public health system, such as Brazil’s Unified Health System (Sistema Único de Saúde [SUS]), encompasses substantial geographic, demographic, and operational heterogeneity, making it an ideal yet challenging environment to evaluate clinical utility and equity of AI tools. Therefore, prospective, multicenter implementation trials that measure the impact of AI on clinician performance and patient management across diverse, real-world settings are essential to establish generalizability, robustness, and fairness prior to widescale adoption [20,21].

The LuAna (Lung Analysis) trial will evaluate whether AI-assisted CXR interpretation improves the detection of radiographic findings in adults with respiratory symptoms or undergoing treatment for respiratory diseases compared with physician-only interpretation within Brazil’s Unified Health System. We hypothesize that AI assistance will enhance diagnostic accuracy, expedite triage, reduce delays, improve cost-effectiveness, and facilitate scalability. If successful, LuAna could become a model for equitable AI integration into diagnostic workflows in LMICs and beyond.

This study aims to evaluate the effectiveness of AI-assisted CXR interpretation in improving diagnostic accuracy, clinical efficiency, and patient outcomes within Brazil’s Unified Health System (SUS). Using a stepped-wedge cluster-randomized design, this protocol aims to investigate whether AI-based decision-support tools enhance general practitioners’ ability to detect predefined radiographic findings in adults presenting with respiratory symptoms or with pulmonary disease compared with unaided interpretation. The trial further seeks to determine AI’s potential to strengthen diagnostic performance in resource-limited settings and inform the implementation of scalable, equitable, and efficient health care.

## Methods

### Algorithm Development

#### Overview

Between 2019 and 2024, 3 independent deep-learning models were developed and internally validated [22]. The “Lung Abnormality” model classified CXRs as either normal or abnormal. The “Radiological Findings” model categorized patterns into predefined classes, including consolidation, pulmonary opacity, pneumothorax, atelectasis, pleural effusion, and cardiomegaly. Finally, the “Tuberculosis” model predicted whether a CXR was suggestive or not suggestive of pulmonary TB. The models were trained on CXRs from adults aged 18 years or older, including both male and female patients. The dataset comprised anteroposterior or posteroanterior views sourced from public databases and from multiple partner health care centers across Brazil, including referral clinics for TB care.

Model predictions were given as probabilities ranging from 0 to 1, with a threshold of 0.5: values of 0.5 or higher were classified as positive, and values below 0.5 as negative. The exceptions are pneumothorax (0.8), consolidation (0.6), and TB (0.4), which had different thresholds determined by the GHOST (generalized threshold shifting) method [23]. Heatmaps highlight regions of interest, contributing to the algorithm’s output (Figure 1).

**Figure 1. F1:**
[figure not shown]
Chest X-ray (CXR) processed by the radiological findings model. (**A**) Original CXR image showing consolidation in the right lower lung field. (**B**) Artificial intelligence–generated output with heatmap highlighting the region with the highest predicted probability of consolidation.

#### Internal Algorithm Validation

Internal validation proved robust performance, with the 3 models showing consistent outcomes across the validation datasets (Table 1). Overall metrics for the models were as follows: the “Pulmonary Abnormality” model achieved an area under the receiver operating characteristic curve (AUC) of 0.82, with an accuracy of 0.82, a sensitivity of 0.82, and a specificity of 0.84. The “Radiological Findings” model reached an overall AUC of 0.82, with per-class performance ranging from 0.77 (atelectasis) to 0.90 (pneumothorax). The “Tuberculosis” model achieved an AUC of 0.81, with an accuracy of 0.81, a sensitivity of 0.83, and a specificity of 0.78. These findings suggest that the models could be suitable for eventual clinical use, though additional testing in prospective real-world clinical settings is still necessary.

**Table 1. T1:** Internal validation dataset values.

Model	AUC^a^	Sensitivity	Specificity	Accuracy
Pulmonary abnormality	0.82	0.82	0.84	0.82
Tuberculosis	0.81	0.83	0.78	0.81
Radiological findings				
Consolidation	0.78	0.84	0.57	0.59
Lung opacity	0.78	0.89	0.50	0.64
Atelectasis	0.77	0.88	0.49	0.57
Cardiomegaly	0.84	0.86	0.67	0.70
Pneumothorax	0.90	0.81	0.85	0.83
Pleural effusion	0.90	0.92	0.70	0.78

a AUC: area under the receiver operating characteristic curve.

#### External Algorithm Validation

An external retrospective validation of 1092 anonymized CXRs, including 586 double-read by thoracic radiologists at Hospital Israelita Albert Einstein, demonstrated variability in model performance. The Pulmonary Abnormality and Tuberculosis models achieved AUC values of 0.89 and 0.84, respectively, whereas the Radiological Findings model showed AUC values ranging from 0.811 to 0.96, as shown in Table 2.

**Table 2. T2:** External validation dataset values.

Model	AUC^a^	Sensitivity	Specificity	Accuracy
Pulmonary abnormality	0.89	0.82	0.84	0.82
Tuberculosis	0.84	0.83	0.71	0.77
Radiological findings				
Consolidation	0.92	0.95	0.70	0.74
Lung opacity	0.91	0.90	0.72	0.80
Atelectasis	0.81	0.55	0.87	0.81
Cardiomegaly	0.95	0.84	0.90	0.90
Pneumothorax	0.96	1.0	0.79	0.80
Pleural effusion	0.95	0.80	0.92	0.90

a AUC: area under the receiver operating characteristic curve.

In the prospective phase of the Radiological Findings model, which included 30 real-time cases, no statistically significant differences were observed. All physicians were provided with standardized CARPL (Clinical AI Research Platform for Labeling) training to promote uniformity in image labeling [24].

Therefore, the current gap between internal and external performance per class of the Radiological Findings model underscores the need for multi-institutional datasets and rigorous real-world testing before clinical adoption. The AI models will be locked for the duration of the trial; no updates to weights or thresholds will be implemented once recruitment starts. Overall, this study underscores both the potential and limitations of AI in radiology, reinforcing that limited real-world evidence warrants caution and that robust validation frameworks are as essential as algorithm development [25-27].

### Study Design: Stepped-Wedge Randomized Design

The stepped-wedge cluster-randomized design was chosen for this trial because of its clear methodological benefits. Unlike parallel designs, all clusters eventually receive intervention, enhancing acceptability in clinical settings where prior evidence suggests potential benefit [28,29]. The phased implementation also mirrors real-world logistical constraints while allowing for both within- and between-cluster comparisons, thereby improving statistical efficiency and power [28,30]. Additionally, repeated measurements over time enable adjustment for secular trends, strengthening causal inference [28-31]. These characteristics make the stepped-wedge design especially suitable for pragmatic evaluations of health care interventions.

This nationwide, multicenter, stepped-wedge cluster-randomized trial (SW-CRT) follows the CONSORT-AI (Consolidated Standards of Reporting Trials-Artificial Intelligence) and SPIRIT-AI (Standard Protocol Items: Recommendations for Interventional Trials-Artificial Intelligence) guidelines [32,33]. It will evaluate whether AI can improve CXR interpretation in routine clinical care across Brazil. Cities will act as clusters, comprising public, private, and philanthropic health care units to ensure broad socioeconomic and geographic representation [28,30,31,34]. All clusters will begin in the control condition (standard physician interpretation) and will cross over to the intervention (AI-assisted physician interpretation) at randomly assigned monthly intervals. Potential contamination across clusters will be minimized by selecting independent clinical units with nonoverlapping staff and workflows.

A batched stepped-wedge approach allows staggered initiation, accommodating operational constraints while minimizing contamination or learning effects. Once a cluster transitions, it remains in the intervention arm (Figure 2). Simple urn-based randomization without replacement will occur independently in each batch. Participating centers within cities must have infrastructure for CXR interpretation (negatoscope or digital screen), reliable internet access, and commitment to study protocols.

**Figure 2. F2:**
[figure not shown]
Study design and implementation flow of the LuAna (Lung Analysis) trial. The LuAna trial uses a batched stepped-wedge cluster-randomized design, where all centers begin in the control phase (gray) with physician-only interpretation. At randomly assigned sequences, clusters are grouped into batches and sequentially cross over to the intervention phase (green). Once a cluster transitions, it remains in the intervention phase until trial completion. At the site level, patient inclusion and physician interpretation occur continuously. During control periods, only the physician’s interpretation is recorded. During intervention periods, physicians first provide their interpretation, after which AI support (LuAna) is introduced. This design ensures staggered, overlapping transitions across centers while maintaining consistent trial procedures. AI: artificial intelligence.

All participating clusters will undergo a site initiation visit (SIV) prior to enrollment. All physician participants will complete the informed consent process and sign the informed consent form. During the SIV, local investigators will receive standardized training on study procedures, data entry, image capture protocols, and use of the study platform (LuAna). Training will include hands-on instruction to ensure the uniform application of inclusion criteria, proper anonymization of patient data, and completion of interpretation forms. Following the SIV, sites will begin patient recruitment and data collection. This study was registered on ClinicalTrials.gov (NCT06686251).

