### Radiograph Eligibility Criteria

#### Inclusion Criteria

Eligible chest radiographs must meet all of the following criteria: it should (1) be of individuals aged 18 years or older; (2) be obtained either during the presence of respiratory symptoms or while the patient is undergoing treatment for a respiratory disease; (3) be any radiograph without a preexisting report at the time of inclusion; (4) be acquired on any X-ray equipment, provided that at least 1 frontal chest view is included; and (5) be performed either during the acute episode of the respiratory condition or throughout the postacute follow-up period, until its completion.

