**Figure 3. F3:**
[figure not shown]
Workflow for chest X-ray (CXR) interpretation in control and intervention groups. Top panel (control group—without AI): CXRs from patients with respiratory complaints are interpreted solely by the physician (1), without access to AI support (2). Bottom panel (intervention group—with AI): physicians first perform an initial assessment of the CXR (1) and register their findings via the LuAna mobile app (2). After this, the AI model processes the image and returns a score and a heatmap highlighting abnormal regions (3). The physician can then review and, if needed, revise their interpretation based on the AI output (4). Both pre- and post-AI interpretations are recorded for analysis. For both groups, CXR assessments are compared against a reference standard, defined as thoracic radiologist evaluation performed on the CARPL, with reports independently double-validated by thoracic radiologists blinded to both the physician assessment and AI output. The primary outcome is the comparison of radiologic findings detection rates before and after AI assistance relative to the reference standard. The workflow includes data acquisition at the study centers, followed by radiologist annotation, primary and secondary end point evaluation, and statistical analysis at the coordinating center. AI: artificial intelligence; CARPL: Clinical Artificial Intelligence Research Platform for Labeling.

Only demographic variables, including age group, sex, and race, will be collected in aggregated form to characterize the study population and allow for fairness analyses, ensuring equitable and unbiased AI performance. CXRs will be captured either by photographing printed films positioned on a lit negatoscope, by photographing digital images displayed on a picture archiving and communication system monitor, or by direct screen capture, all following strict protocols to guarantee full anonymization. Physicians will capture only the thoracic image, ensuring that all patient identifiers are systematically removed and never visible. A patient ID entered solely to return the radiologist’s report to the local health unit will be encrypted and remain inaccessible to the research team. Nondiagnostic images or studies failing predefined quality-control criteria will be excluded from analysis.

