### Reference Standard Generation, Report Return, and Critical Findings

The radiologists are responsible for producing the ground-truth (reference standard) for all CXR images during the study. The first step in ground-truth generation is to assign 2 thoracic radiologists to independently interpret the CXR images to set up the reference standard, classifying each finding as “normal” or “abnormal.” The correct classification matches the reference standard. For cases classified as *abnormal*, the presence or absence of the relevant radiological findings (consolidation, pulmonary opacity, pneumothorax, atelectasis, pleural effusion, and cardiomegaly) will be assessed, as well as the presence or absence of changes suggestive of TB. Based on these evaluations by the 2 thoracic radiologists, the ground truth is established. The radiologists will be blinded to both the physicians’ interpretations and the AI outputs.

A chest radiograph will be labeled as suggestive of pulmonary TB if at least 1 radiographic feature considered compatible with pulmonary TB is present, as determined by the adjudicated thoracic radiologist reference standard. Examples include cavitation, upper-lobe–predominant consolidation or opacities, fibronodular changes or scarring with upper lobe volume loss, or a miliary pattern. If none of these features is present, the examination will be labeled as “not suggestive of pulmonary TB.”

For physician performance analyses, an examination will be considered correctly classified when the physician’s binary classification (normal vs abnormal; suggestive vs not suggestive of pulmonary TB; presence or absence of specific radiographic patterns) matches the adjudicated thoracic radiologist reference standard. In cases of any disagreement between the 2 experts in any of the evaluated items, a third radiologist, more senior, will adjudicate.

All findings will be registered in the CARPL, with abnormalities annotated to allow direct comparison with AI outputs. This will serve as the reference value for model validation and performance analysis (Figure 4).

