### Statistical Analysis

The sample size was calculated to detect a minimum difference of 10% in the primary outcome—a binary indicator of whether the physician correctly labeled a CXR—between the AI-assisted and control groups. The calculation accounted for the stepped-wedge cluster-randomized design with batched implementation using the following assumptions: 9 clusters randomized in 3 batches to cross over from control to intervention, 10 time periods, a baseline detection rate of 67% in the control group, an expected increase to 77% in the intervention group, and an intracluster correlation coefficient ranging from 0.001 to 0.003.

The design effect was adjusted for the correlation structure induced by repeated measures within clusters over time using methods described by Hussey and Hughes [28] and extended to account for batched randomization, as described by Hemming et al [35,36]. The power calculation targeted 80% power at a 2-sided significance level of 5% and accounted for potential variability in cluster sizes. The final average cluster size was 37, and the overall sample size was inflated by 10% to account for anticipated exclusions due to image quality issues or missing data (dropout). This approach ensures adequate power to detect a meaningful effect of the intervention while maintaining the integrity of the stepped-wedge design with staggered implementation across batches.

Primary analysis will follow the modified intention-to-treat principle. All eligible CXRs (the unit of analysis in this study) will be analyzed according to the study group (control or intervention), to which their corresponding cluster was allocated at the time of image acquisition, regardless of physician adherence to the intervention or exposure to AI output. Images of poor quality, as defined by our radiologists, will be excluded postrandomization.

The primary outcome analysis will use a generalized linear mixed model with a binomial distribution and logit link function to estimate the effect of the AI-assisted intervention on detection probability. The model will include fixed effects for the intervention group (AI-assisted vs control), calendar time (to adjust for secular trends), time since intervention rollout (to account for learning or adaptation effects), and batch effects. In addition, random intercepts for clusters will be specified to account for intracluster correlation.

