### Ethical Considerations

This study was reviewed and approved by the local Ethics Committee of Hospital Israelita Albert Einstein (CEP Einstein), São Paulo, Brazil, registered under IRB00005041, in accordance with applicable national and international regulations (CAAE number 82494524.0.1001.0071). A waiver of written informed consent for patients was granted, as the study is strictly observational and involves no intervention in routine clinical care, no modification of clinical management, and no access to patients’ medical records. Only chest radiographs obtained as part of standard care were used, and all images were fully anonymized prior to storage and analysis, with no directly identifiable information included in the research dataset. However, written informed consent was obtained from the physicians responsible for enrolling patients in the LuAna trial, as they are considered direct research participants.

All data are handled under strict confidentiality procedures. Chest radiograph images were collected via the LuAna app and stored in an anonymized format on a secure cloud-based server.

The analytical database contains exclusively deidentified data. Access to identifiable information at the study sites, when applicable, is restricted to authorized local investigators. Study data will be securely stored at the hosting institution for a minimum of 5 years, in compliance with institutional and regulatory requirements.

Posttrial access pathways for the tool will be discussed with the Brazilian Ministry of Health to ensure continuity if the intervention proves beneficial. Technical details of the algorithm, including its development, training, validation, and performance characteristics, will be described in accordance with the CLAIM (Checklist for Artificial Intelligence in Medical Imaging) reporting guidelines [40], complementing the CONSORT-AI and SPIRIT-AI standards applied to the clinical trial components [32,33].

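### A change in film mix at a city's crossover would be counted as an AI effect: physicians who know the phase enrol the films, and the primary model has no film-level term

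*Protocol article*

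**What the plan says.** **Who brings films in.** Ethical Considerations describes the consenting readers as the "physicians responsible for enrolling patients in the LuAna trial". Data Collection states: "Physicians will capture only the thoracic image". The reader is thus also the recruiter. The Figure 2 caption says that at site level "patient inclusion and physician interpretation occur continuously"; this describes timing, not sampling.

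**Which films qualify.** Eligibility is wide. One criterion is that the film "be any radiograph without a preexisting report at the time of inclusion", and films from acute episodes and from follow-up both count. The stated safeguard on inclusion is training at the site initiation visit, intended to secure "uniform application of inclusion criteria".

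**Knowledge of phase.** AI output is shown only in intervention periods, so physicians know which phase they are in.

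**The primary model.** Statistical Analysis says: "The model will include fixed effects for the intervention group (AI-assisted vs control), calendar time (to adjust for secular trends"; it then adds time since rollout, batch and a random cluster intercept. No covariate describes the film. Image characteristics enter only a separate model of the algorithm's output. The robustness analyses in the Discussion (image quality, artifacts, devices) are presented as checks on the AI model.

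**What is available for adjustment.** "The radiologists are responsible for producing the ground-truth (reference standard) for all CXR images during the study", and these radiologists are blinded to the physicians' reads and the AI output. In intervention periods, "Both pre- and post-AI interpretations are recorded for analysis".

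**The concern.** When recruiters know the phase, the cases they bring in can differ before and after crossover. Physicians might upload harder films once AI help is offered, or more obviously abnormal ones. Accuracy depends on the film, so the observed rate can then change with no AI effect at all.

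The planned terms do not remove this. Calendar time takes out changes common to all cities, and the cluster intercept takes out stable differences between cities. A step at each city's own crossover coincides with the intervention indicator. The primary comparison could show a benefit that is not there, or hide one that is.

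**Working it through.** **The plan's own figures.** The design assumes 67% in control and 77% with AI: a difference of 10 points and an odds ratio of (0.77/0.23)/(0.67/0.33) = 1.65. The stated 80% power cannot be reproduced uniquely, because the layout figure is not shown and the article does not say whether the average size of 37 is per cluster or per cluster-period. With 37 per cluster-period and a batch term, a Hussey-Hughes calculation gives about 72% to 96% across plausible layouts. With 37 per cluster in total it gives 13% to 27%. The point does not depend on this, except that step 4 uses the standard error implied by 80% power.

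**Step 1. Size of a mix shift.** Take a correct reading as agreement with the reference standard. Let s be the share of reference-abnormal films:

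accuracy = (1 − s) × accuracy on normal films + s × accuracy on abnormal films.

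The documents give no accuracies by film type. The pairs below are assumptions, each chosen to return 67% at s = 0.5.

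| Assumed normal / abnormal accuracy | s = 0.5 | s = 0.6 | s = 0.7 |
|---|---|---|---|
| 75% / 59% | 67.0% | 65.4% (−1.6 points) | 63.8% (−3.2) |
| 80% / 54% | 67.0% | 64.4% (−2.6) | 61.8% (−5.2) |
| 85% / 49% | 67.0% | 63.4% (−3.6) | 59.8% (−7.2) |

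In general, apparent effect = accuracy gap between film types × shift in mix. Gaps of 20, 30 and 40 points with a 10-point shift give 2, 3 and 4 points. The sign reverses if easier films come in after crossover.

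**Step 2. On the odds-ratio scale.** Assume easy films are read at 82% and hard films at 52%, mixed 50:50 (67% overall), with no AI effect.

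- Easy share rises to 60%: 0.6 × 0.82 + 0.4 × 0.52 = 0.70. Odds ratio (0.70/0.30)/(0.67/0.33) = 1.15.
- Easy share rises to 70%: 0.7 × 0.82 + 0.3 × 0.52 = 0.73. Odds ratio (0.73/0.27)/(0.67/0.33) = 1.33.

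**Step 3. Do the planned terms absorb it?** In this set-up the expected rate takes one value before crossover and another after it. The intervention indicator alone fits that exactly, so the calendar-time and time-since-rollout coefficients are zero. A fit to the expected data confirmed this: intervention odds ratios of 1.15 and 1.33, and 1.00 per period for time since rollout. With film type added, the intervention odds ratio returned to 1.00, because the added covariate was the very one that produced the shift.

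**Step 4. Effect on the test.** Suppose the standard error is the one that gives exactly 80% power: 0.10/(1.960 + 0.842) = 0.0357. A 3-point bias is then 0.84 standard errors and raises the two-sided false-positive rate from 5% to 13%. A 6-point bias is 1.68 standard errors and raises it to 39%.

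**Step 5. Dependence on the outcome definition.** The Objective, the reference-standard section and Statistical Analysis treat the outcome as per-examination accuracy or a correct label. The Primary Outcome section instead scores correct identification of any of the five findings. Read literally:

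- A film with none of the five findings always scores 0. At a 50:50 mix the rate could not exceed 50%, so 67% would be impossible.
- More abnormal films would raise the rate, the opposite of step 1.
- A normal/abnormal term would separate completely in a logit model.

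The Figure 3 caption describes a before-and-after contrast, which within a film is immune to mix.

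**The case against.** The strongest reply is that the point rests on silence in a condensed article. Nowhere does it say that physicians may choose among eligible films, and continuous inclusion does not imply choice. A consecutive rule, screening logs and tables of mix by phase may sit in the full protocol. This stands: discretion over uploads is an inference. It does not answer the model, whose terms are stated here.

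The incentive may also be weak. AI output comes only after the first read and the physician's management decision, and the Figure 4 workflow returns radiologist reports to sites without distinguishing phases. That makes a large shift less likely but does not rule one out.

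Part of the check may already be planned. The secondary objectives include physician learning before and after the intervention, and the Discussion foresees a longitudinal analysis of independent performance. Neither is specified as a check on the primary comparison.

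Three stronger readings are tempting but unsupported:

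- That a consecutive rule could not be verified because patient IDs are hidden from the research team. Counts of eligible and uploaded films kept at the sites would suffice, and Ethical Considerations allows authorised local investigators access to identifiable data.
- That the same adjustment works whatever the endpoint. Step 5 shows that it does not.
- That adjusting for reference labels removes the whole bias. Labels record which findings are present, not how subtle they are.

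**Conclusion.** The point holds as a gap in the primary model. Physicians who know the phase supply the films, no consecutive rule is stated here, and no planned term separates a mix change at a city's own crossover from the AI effect. The documents do not show that such a shift will occur, and with no shift there is no bias.

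The illustrative size is about 2 to 4 points per 10-point change in mix. This rests entirely on assumed accuracies, an assumed mix and an assumed shift, with direction unknown. Reproducing the full 10-point target would take a shift of about 33 points at a 30-point gap (0.30 × 0.333 = 0.10). The realistic risk is therefore distortion of the estimate and of the error rate, rather than a wholly spurious target effect. The step 1 figures apply only if the outcome is per-examination agreement with the reference standard.

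**What to change.** 1. **Adjust the primary model.** With the outcome taken as per-examination agreement with the reference standard, add the blinded reference-standard categories (normal/abnormal and which of the five findings are present) as fixed effects. Report a risk difference standardised over the film mix beside the odds ratio. If the any-of-five definition is kept, restrict the analysis to films with at least one reference finding, adjust for which findings are present, and omit the normal/abnormal term because it would separate completely. The outcome definitions must be reconciled first.
2. **Prespecify a check.** Fit the same model to control reads versus the pre-AI first reads of the intervention phase. Neither set is AI-assisted on the film in question, so this works under any outcome definition. A difference signals a case-mix shift (including difficulty shifts that the labels miss), changed effort or learning. It cannot tell these apart.
3. **Report the reference-standard film mix by phase.**

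**Cost.** Analysis-plan wording only, since the labels and the first reads are already collected. The model gains a few parameters. The conditional odds ratio changes through non-collapsibility, which is why the standardised difference must accompany it. Differences in difficulty within a finding category remain unadjusted, and the report should say so.
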